## **1. Administrative Information**

### **1a – Title and trial registration - Descriptive**

Statistical analysis plan for the Algofine-2 study (« Intranasal Sufentanil analgesia versus Morphine intravenous in Emergency room »): A multi-center, randomized, controlled, double-blind, double placebo trial.

### **1b – Title and trial registration - Trial registration number**

Trial Registration : EudraCT registration number : 2013-001665-16, Date 2013-08-01

### **2 – SAP version**

Version 3.0 of the statistical analysis plan was carried out after the blind review of May 12, 2016 in the presence of [name] (Investigator, coordinator of the study), [name] (Scientific Manager of the study), [name] (CRA, Project Manager), [name] (CCA) and [name] (Biostatistician), in accordance with the database freezing procedure.

This analysis plan was presented during the methodology EPP staff (Evaluation of Professional Practices) of the CIC of June 27, 2016. A sensibility analysis has been proposed, in accordance with the latest JAMA recommendations, to complete the analysis of the primary endpoint performed on the per protocol population by validating the results on the Intent to Treat (ITT) population.

### **3 – Protocol version**

This document has been written based on information contained in the study protocol MS4 version 10, dated October 22nd, 2015.

### **4a – SAP revisions - History**

| Protocol version | Updated SAP Version number | Section number changed | Description of and reason for change                                                       | Date |
|-------------------------|-----------------------------------|-------------------------------|---------------------------------------------------------------------------------------------------|-------------|
| 7.0                     | 1.0                               | -                             | Initial submission of the protocol to the Ethics Comity (French CPP) and French ANSM authorities. | 31/07/2013  |

|            |     |                                                             |                                                                                                                                                                                                                                                                                                                                                                                                                                                                              |            |
|------------|-----|-------------------------------------------------------------|------------------------------------------------------------------------------------------------------------------------------------------------------------------------------------------------------------------------------------------------------------------------------------------------------------------------------------------------------------------------------------------------------------------------------------------------------------------------------|------------|
| 8.0
MS2 | 2.0 | - Summary
Section "main
judgment
criterion"        | - Clarification of the main judgment criterion :
Variation of the numerical scale of pain (EN at T30-
EN at T0)                                                                                                                                                                                                                                                                                                                                                        | 29/04/2014 |
|            |     | - Summary
Section "target
population"                 | - Clarification of the target population: distinction
between the analysis population related to the
main objective (2x110) and that linked to the
secondary objective n°5 (30 complementary
subjects).                                                                                                                                                                                                                                                          |            |
|            |     | - Summary
Section "Data
processing"                   | - Precision for the non-inferiority analysis: the
threshold selected for this analysis will be 1.3.

- Precision for the statistical threshold of
significance retained for the non-inferiority analysis
(2.5%).

- General description of the descriptive and
comparative analysis of secondary objectives.                                                                                                                                         |            |
|            |     | - Chapter II
Section
"Objectives"                     | - Modifications and addition of objectives and
secondary criteria.                                                                                                                                                                                                                                                                                                                                                                                                        |            |
|            |     | - Chapter IV
Section "sample
size"                    | - Changes in sample size calculation: Change in the
common standard deviation (2.1 to 2.8) related to
the main criterion based on the publication
"Birnbaum A., Esses D., Randomized Double-Blind
Placebo-Controlled Trial of Two Intravenous
Morphine Dosages (0.10 mg/kg and 0.15 mg/kg) in
Emergency Department Patients With Moderate to
Severe Acute Pain. 49:445-453 (2007)" and the
reduction of the power of the analysis to 80%. |            |
|            |     | - Chapter IX
Section
"Replacement of
missing data" | - Clarification on the replacement of missing data:
For per-protocol population analysis, no
replacement of missing data is considered for the
analysis of the primary endpoint.

With regard to a possible intention-to-treat
analysis, a multiple imputation method would be
implemented.                                                                                                                                                             |            |
|            |     | - Chapter IX
Section
"Statistical tests"              | - Clarification of Statistical Analysis: For each
objective of the study, details of the statistical tests
used and their justifications.

- Precision: A detailed analysis plan covering all
objectives may be completed before the study
database is frozen, in conjunction with the scientific
steering committee of the study.                                                                                                                      |            |

|   |     |                             |                                                                                                                                                                                                                                                                             |            |
|---|-----|-----------------------------|-----------------------------------------------------------------------------------------------------------------------------------------------------------------------------------------------------------------------------------------------------------------------------|------------|
| - | 3.0 | "Superiority analysis"      | - Clarification of Statistical Analysis: The evaluation of the superiority of intra-nasal Sufentanil compared to the reference treatment will be used if non-inferiority is demonstrated.                                                                                   | 12/05/2016 |
| - | 3.1 | "Primary endpoint analysis" | - Clarification of Statistical Analysis: A sensibility analysis has been proposed by the methodology EPP staff to complete the analysis of the primary endpoint performed on the per protocol population by validating the results on the Intent to Treat (ITT) population. | 27/06/2016 |
| - | 3.2 | -                           | SAP reviewed to take account of the new Guidelines (JAMA, 2017).

- Clarification of Statistical Analysis: The reviewer of the manuscript proposed to complete the analysis with a linear regression that adjusts for baseline pain score and site                    | 13/05/2019 |

#### 4b – SAP revisions - Justification for each SAP revision

The statistical analysis plan (SAP) of the clinical protocol has been updated April 29, 2014, to adapt it to:

- the clarification of the main judgment criterion : Variation of the numerical scale of pain (EN at T30 – EN at T0),
- precision for the non-inferiority analysis : the threshold selected for this analysis will be 1.3.
- precision for the statistical threshold of significance retained for the non-inferiority analysis (2.5%).
- general description of the descriptive and comparative analysis of secondary objectives.
- the clarification of the target population : distinction between the analysis population related to the main objective (2x110) and that linked to the secondary objective n°5 (30 complementary subjects).
- the modifications and addition of objectives and secondary criteria.
- the modification of the sample size according to the change in the common standard deviation (2.1 to 2.8) related to the main criterion based on the publication "*Birnbaum A., Esses D., Randomized Double-Blind Placebo-Controlled Trial of Two Intravenous Morphine Dosages (0.10 mg/kg and 0.15 mg/kg) in Emergency Department Patients With Moderate to Severe Acute Pain. 49:445-453 (2007)*" and the reduction of the power of the analysis to 80%.

- Clarification on the replacement of missing data: For per-protocol population analysis, no replacement of missing data is considered for the analysis of the primary endpoint.
- With regard to a possible intention-to-treat analysis, a multiple imputation method would be implemented.
- Clarification of Statistical Analysis: For each objective of the study, details of the statistical tests used and their justifications.
- Precision: A detailed analysis plan covering all objectives may be completed before the study database is frozen, in conjunction with the scientific steering committee of the study.

The Statistical Analysis Plan (SAP) of the clinical protocol was updated after the blind review on May 12, 2016, in accordance with the database freezing procedure, to incorporate a superiority analysis on the Intent to Treat (ITT) population in case of non-inferiority demonstration.

The Statistical Analysis Plan (SAP) of the clinical protocol was updated after the methodology EPP staff (Evaluation of Professional Practices) of the CIC of June 27, 2016. A sensibility analysis has been proposed, in accordance with the latest JAMA recommendations, to complete the analysis of the primary endpoint performed on the per protocol population by validating the results on the Intent to Treat (ITT) population.

The statistical analysis plan for this randomized trial was formatted May 13, 2019 to conform to the 2017 version of the recommendations “Guidelines for the content of statistical analysis plans in clinical trials” (JAMA, 2017).

#### 4c – SAP revisions - Timing of SAP revisions in relation to interim analyses

Not applicable.

## 2. Introduction

### 7 – Background and aim

Analgesia is one of the main objectives of the management of patients presenting in an emergency department. The traumatology is more particularly associated with acute pain episodes, this is the case at the time of the trauma but also when the traumatized area is solicited (removal of clothing, clinical or radiological examination). The Grenoble basin and the Alpine arc have the dual feature of being both densely populated in terms of population and geographically located very close to mountain areas. As a result, in addition to "classical" sports and domestic traumatology, mountain sports, and in particular winter sports, are added. If the pain symptom is particularly associated with trauma, it is also very often underestimated, which can have deleterious consequences on the clinical state of the patients.

Reducing these post-traumatic acute pain episodes is one of the public health goals that has been clearly defined by the Ministry of Health.

Other products derived from the Morphine are usable and have a theoretical interest because they act faster. This is the case of Sufentanil, which has a shorter reaction time (60 to 120 seconds) than Morphine.

In addition, Sufentanil has the advantage of a wider therapeutic margin than Morphine or Fentanyl. In practice, the studies carried out reveal little undesirable effects when using Sufentanil, often at doses higher than the equi-analgesia Morphine.

Studies published so far tend to show the efficacy and safety of Sufentanil used intranasally in the management of pain in emergencies. However, there are no randomized, controlled, blinded, emergency department studies in an adult population.

(Nota: from the Paragraph “justification of the study” of the protocol)

#### 8 – Objectives

The main objective of the study is to compare the efficacy of analgesia performed by intranasal Sufentanil compared to the reference treatment (IV Morphine).

The aim of the secondary objectives of the trial is to :

- Compare the efficacy of analgesia performed by intranasal Sufentanil compared to the reference treatment (IV Morphine) after 10 min and 20 min of treatment.
- Evaluate the efficacy of analgesia performed by intranasal Sufentanil and Morphine IV, after 10 min and 20 min of treatment.
- Compare the occurrence of adverse effects between treatment groups (Sufentanil IN versus Morphine IV).
- Evaluate the efficacy of analgesia performed by intranasal Sufentanil compared to the reference treatment (IV Morphine) after 10 min, 20 min and 30 min of treatment in the group of pre-hospital patients.
- Evaluate patient satisfaction

### **3. Study Methods**

#### **9 – Trial Design**

This study is a multicentre prospective, randomized, double-blind, controlled, double placebo trial.

#### **10 – Randomization**

Randomization 1:1 in parallel groups was pre-performed in blocks of random sizes and stratified by centre. The randomization list was handed over to the central pharmacy in charge of preparing packs. The randomization list was generated using the Nquery Advisor software version 7.0 (Statistical Solutions Ltd, Boston MA, USA).

#### **11 – Sample size**

##### **Version 1.0 of July 31 2013 [name] (Protocol version 7.0 – 31/07/2013):**

The number of patients to be included in the study was calculated for a non-inferiority study according to the following assumptions: The mean value of EN at 30 minutes in patients with pain  $\geq 6$ , relieved by Morphine is 3.7 (standard deviation of 2.2). Given an alpha risk of 2.5% and a non-inferiority threshold of 1.3 (EN standard equivalence threshold usually accepted). The number of subjects required, calculated using the Schuirmann method, is 99 in each group to be able to conclude that the evaluated treatment is non-inferior compared to the reference treatment on EN at 30 minutes with a power of 97%.

Taking into account the fact that this study is multi-centric and considering that 10% of the randomized patients are likely not to fulfill the criteria of the per protocol analysis, the total number of the study is therefore 220 patients (110 in each case group).

##### **Version 2.0 of April 29, 2014 [name] (Protocol version 8.0 – 29/04/2014):**

This study will involve a sample size of 198 patients (99 patients per group). In order to guarantee this number of analyzable patients, we envisage a complementary recruitment of 10 patients per group. The calculation of the number of patients required corresponds to a non-inferiority study design.

The null hypothesis corresponds to a difference in efficacy between treatment groups above the equivalence threshold; The alternative hypothesis allows us to conclude that the treatments are equivalent;

The primary endpoint is the difference, before / after, of the mean pain score assessed by a numerical scale at inclusion and 30 minutes after administration.

The number of subjects required was assessed by the Schuirmann method, taking into account a minimal, clinically significant value of pain level evolution defined a priori as a modification of 1.3 of the numerical scale (EN), an alpha risk of 2.5% and a standard deviation of the response of 2.8.

A total of 99 subjects per group will thus be necessary to reject the null hypothesis of a difference in efficacy and to conclude that the evaluated treatment is not inferior compared to the reference treatment, in terms of the evolution of EN in the first 30 minutes, with a power of 80%.

This calculation was performed using the NQuery Advisor software version 7.0 (Statistical Solutions Ltd., Boston MA, USA).

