#### Post-hoc analysis of the power of the study :

The recruitment was lower than expected over the planned duration of the study and the power remained above 80% with an effective standard deviation in reduction in pain by 2.1 in post-hoc analysis.

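### The 80% power stated for non-inferiority at 99 per group is the power of the two-sided equivalence test; non-inferiority has about 90% if the true difference is 0, which the SAP does not state

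*SAP*

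**What the plan says.** Section 11, Version 2.0, first declares the design: "The calculation of the number of patients required corresponds to a non-inferiority study design". It then writes the hypotheses as for an equivalence trial: "The alternative hypothesis allows us to conclude that the treatments are equivalent". The method is also one for equivalence: "The number of subjects required was assessed by the Schuirmann method". The inputs are a margin of 1.3 points on the numerical pain scale (EN), "an alpha risk of 2.5% and a standard deviation of the response of 2.8". The result is attached to a non-inferiority conclusion: "A total of 99 subjects per group will thus be necessary to reject the null hypothesis of a difference in efficacy" and to declare sufentanil not inferior to morphine, at a power of 80%.

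Elsewhere in the SAP:

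- Section 12 fixes the test framework as non-inferiority.
- Section 27a announces a one-sided test for the primary analysis but carries it out with a mean-equivalence routine (tostt) over a symmetric interval.
- Section 29 repeats a Schuirmann test for the ITT sensitivity analysis.
- The post-hoc paragraph of Section 11 reports that recruitment fell short and that "the power remained above 80% with an effective standard deviation in reduction in pain by 2.1 in post-hoc analysis".

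**The concern.** Non-inferiority and equivalence are different claims, and the same sample has different power for each. Equivalence needs both confidence limits inside ±1.3; non-inferiority needs only the limit on the unfavourable side. A power figure for one is not a power figure for the other, and the number described as necessary depends on which is meant.

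The two claims can also give different answers. If sufentanil were better by enough that the interval passed 1.3 in its favour, the symmetric procedure would fail although non-inferiority was plainly shown. Section 29 plans a superiority test after non-inferiority, so the SAP itself contemplates an advantage.

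The stated 80% is also the level against which the post-hoc paragraph judges the recruitment shortfall, yet that paragraph does not say what its own figure refers to.

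**Working it through.** **Inputs.** Margin Δ = 1.3, SD σ = 2.8, α = 2.5% (taken as one-sided, per test) and n = 99 per group, all from Section 11, Version 2.0; 1:1 allocation from Section 10. The true difference d is not stated; d = 0 is an assumption, varied in step 4.

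SE = σ√(2/n) = 2.8 × √(2/99) = 0.398, and Δ/SE = 1.3/0.398 = 3.27.

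**1. Reproducing the plan's figure (equivalence, TOST).**
- Normal approximation: 2Φ(3.27 − 1.96) − 1 = 2 × 0.904 − 1 = 80.9%.
- Exact, with t critical values on 196 df and integrating over the sampling distribution of the pooled SD: 80.3%.
- The smallest n reaching 80% is 99 (98 gives 79.7%).

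The plan's 99 and 80% are therefore reproduced exactly as equivalence power at d = 0.

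**2. The same inputs for one-sided non-inferiority.**
- Normal approximation: Φ(3.27 − 1.96) = 90.4%.
- Noncentral t (196 df, noncentrality 3.27): 90.2%.
- The smallest n reaching 80% is 74 (80.1%; 73 gives 79.6%).

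Halving α to 1.25% does not rescue the stated figure: non-inferiority power is then 84.2%.

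**3. Cross-check on Version 1.0** (SD 2.2, 99 per group, stated power 97%). SE = 2.2 × √(2/99) = 0.313 and Δ/SE = 4.16. Exact TOST power is 97.05%, and 99 is the smallest n reaching 97%. Non-inferiority power is 98.5%. Both versions match TOST at exactly n = 99.

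**4. Dependence on the true difference.** One-sided non-inferiority, 99 per group, SD 2.8, noncentrality (1.3 − d)/0.398:

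| True deficit of sufentanil, d | Power |
|---|---|
| 0 | 90.2% |
| 0.1 | 85.1% |
| 0.2 | 78.5% |
| 0.3 | 70.6% |

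**5. The post-hoc statement** (SD 2.1, d = 0 assumed):

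| n per group | Non-inferiority | TOST |
|---|---|---|
| 42 | 80.1% | 60.1% |
| 50 | 86.5% | 73.1% |
| 56 | 90.1% | 80.2% |
| 60 | 92.0% | 83.9% |

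Power of 80% needs 42 per group for non-inferiority and 56 for TOST. From 42 to 55 per group the statement is true for one test and false for the other; from 56 upward it is true for both. The SAP does not give the achieved number.

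**The case against.** The strongest reply is that 80% is not a miscalculation. Section 11 names Schuirmann's method and writes an equivalence alternative, Section 27a runs a symmetric TOST, and Section 29 repeats it for ITT. For that procedure, 99 per group and 80% are correct. This stands: the number is right for the procedure named and wrong for the conclusion and framework to which it is attached.

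It is also fair that the slip is conservative. Whenever TOST rejects, non-inferiority follows, so under the same assumptions power for non-inferiority is at least the stated 80%. A reader might infer that the trial was wrongly sized or its type I error inflated; neither follows.

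A reader might also take 74 per group as the proper benchmark for judging recruitment. That holds only at d = 0. With a true deficit of 0.1 or 0.2, 80% non-inferiority power needs 87 or 103 per group, and 74 per group gives 73.6% or 66.1%.

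Finally, a reader might infer that the post-hoc sentence repeats the mix-up between the two tests. The documents do not show this, because the sentence names no test. What can be said is that it omits the sample size, the test and the assumed difference. It is true that the Table 2 template in Appendix I already provides for n per group and a 95% interval for the group difference, so the information that should replace the sentence is already planned.

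**Conclusion.** The point holds as a mislabelled power figure resting on inconsistently stated hypotheses. At a margin of 1.3, SD 2.8, one-sided 2.5% and 99 per group, 80% is equivalence power (80.3%). Non-inferiority power is about 90% if the true difference is 0, and 85%, 79% or 71% at a true deficit of 0.1, 0.2 or 0.3 points. At a true difference of 0, 99 per group is 25 more than the 74 needed for 80% non-inferiority power, so the word necessary does not fit the stated conclusion. The SAP gives no true difference; the exact match of both versions to TOST at zero makes that the likely working assumption.

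The post-hoc power statement cannot be checked as written, and the documents do not show it to be false. Severity is moderate: the trial is not undersized by this error, and the remedy is a matter of consistent definition and reporting.

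**What to change.** 1. **Name one hypothesis throughout.** Since Section 12 adopts non-inferiority, write a one-sided alternative in Section 11. In Sections 27a and 29, base the primary and ITT conclusions on the single one-sided 2.5% test. With the difference defined as sufentanil minus morphine in EN change (T30 − T0), this means that the upper limit of the two-sided 95% confidence interval lies below 1.3. Restating the power in Section 11 alone would leave the equivalence alternative and the symmetric TOST in conflict with Section 12.
2. **Restate the power in Section 11**, for example: *99 per group gives about 90% power for non-inferiority assuming a true difference of 0; the 80% figure is for two-sided equivalence.*
3. **Replace the post-hoc power sentence** with the number analysed per arm and the 95% confidence interval set against the margin.

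The one-sided test is met whenever TOST is met, and sometimes when TOST is not. The current SAP version postdates manuscript review (Section 4a), so the change should be dated and logged as such, with both confidence limits reported so that a reader can see whether the choice of test mattered.

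The cost is SAP wording and reporting only, with no additional patients or data.
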